## Abstract

**Background**: Inflammatory bowel diseases (IBD), associated with a significant burden on patients’ lives, are becoming increasingly common. Patients with IBD need continuous treatment and lifelong monitoring, which could be achieved by telemonitoring. Telemonitoring has been shown to be effective in improving outcomes for patients with IBD, and can provide a more convenient and accessible way for patients to receive care. However, the certainty of evidence remains low. This article outlines the methodology of a randomized control study that aims to assess the efficacy of telemonitoring compared to face-to-face follow-up for patients with IBD in Russia, hypothesizing that the implementation of telemonitoring will lead to improvement in clinical, social, and organizational areas. **Methods:** The TIGE-Rus study is a randomized controlled trial. The study consists of three stages, including selection of patients and random assignment into two groups with a ratio of 1:1, follow-up care using telemonitoring or face-to-face appointments, and evaluation and comparison of follow-up efficacy in both groups. In the first stage, all patients will undergo laboratory tests and instrumental examinations, and fill out questionnaires to measure disease activity, quality of life, medication adherence, psychological well-being, and satisfaction with medical care. In the second stage, the control group will receive standard care while the telemonitoring group will have access to a web platform where they can report their clinical activity, fill out questionnaires, and have online consultations with gastroenterologists. The gastroenterologists will also make monthly phone calls to each patient in the telemonitoring group to monitor their progress. In the third stage of the study, both the telemonitoring group and the control group will be re-hospitalized after six months of monitoring. IBD activity will be evaluated through laboratory and instrumental examinations. Additionally, all the participants will complete questionnaires to assess the disease activity, medication adherence, quality of life, psychological well-being, and satisfaction with medical care in both groups. **Conclusions**: The trial will explore whether telemonitoring is effective in improving clinical, social, and organizational aspects in the management of patients with IBD in the setting of the Russian healthcare system.

## 1. Introduction

Inflammatory bowel diseases (IBD), such as Crohn’s disease (CD) and ulcerative colitis (UC), are chronic conditions characterized by recurrent inflammation of various parts of the gastrointestinal tract. The increasing prevalence and incidence of IBD [1,2], combined with the nature of the disease course, creates a significant medical, social, and financial burden [3]. Even after achieving remission, patients may still experience symptoms such as stool disorders, abdominal pain, and weakness, leading to reduced ability to work and socialize, deterioration of quality of life, and psychological distress [4].

The Selecting Therapeutic Targets in Inflammatory Bowel Disease (STRIDE II) consensus in 2021 recommended that the endpoint for treatment should not only be clinical remission but also improvement in health-related quality of life (QoL), which could be achieved by continuous lifelong follow-up [5]. However, longitudinal face-to-face follow-up is resource-intensive [3], encouraging the development and implementation of innovative solutions and online tools, including telemedicine technologies (TMT) [6], large language models [7], artificial intelligence, and machine learning [8].

Telemonitoring has been shown to be effective in improving outcomes for patients with IBD [9]. Additionally, telemonitoring can provide a more convenient and accessible way for patients to receive care, as they can communicate with their healthcare provider from the comfort of their own homes. According to a systematic review by Al Khoury et al., IBD patients have a positive attitude towards the use of TMT and expect it to be included into their treatment program [10]. A meta-analysis by Pang et al. demonstrated that TMT significantly improved the QoL associated with IBD (*p* = 0.002) [11]. According to Cross et al., IBD patients in the telemonitoring group had a lower risk of hospitalization in comparison with the standard-care group [12]. However, previous studies estimated ad hoc endpoints that despite their value did not provide a complex assessment of social, organizational, and clinical aspects. To address this gap, before the start of the trial we defined the list of assessed parameters by the Delphi method [13]. In our study, we consider the individual with IBD not only as a patient but also as a person and a consumer of medical services.

Our study hypothesizes that the implementation of TMT in patient monitoring will lead to improvements in three key aspects:(i)Clinical aspects: a reduction in the number of relapses and in disease activity;(ii)Social aspects: improvements in QoL and psychological well-being;(iii)Organizational aspects: higher adherence to treatment and satisfaction with medical care.

Additionally, the study hypothesizes that patients’ QoL will be influenced by both the clinical course of the disease and their psychological well-being.

This article outlines the methodology of a randomized control study that aims to assess the efficacy of telemonitoring compared to face-to-face follow-up for patients with IBD in Russia.

### Objectives

The primary objective of this study is to assess the impact of telemonitoring on quality of life (QoL) in patients with inflammatory bowel disease (IBD). Secondary objectives include evaluating disease activity, the incidence of IBD relapses, and the rate of leukopenia in patients receiving immunomodulatory treatments (e.g., thiopurines, cyclosporine, tacrolimus). Additionally, the study will investigate medication adherence, psychological well-being, and patient satisfaction with medical care in the telemedicine group, compared to the face-to-face follow-up group. Finally, we aim to explore the relationship between secondary outcomes and QoL.

## 2. Materials and Methods

This trial protocol follows the SPIRIT (Standard Protocol Items: Recommendations for Interventional Trials) 2013 guidelines [14]. The trial will be conducted in compliance with The International Council for Harmonization of Technical Requirements for Pharmaceuticals for Human Use Good Clinical Practice (ICH GCP). The trial is registered on Clinicaltrials.gov in August 2023, NCT05994716.

### 2.1. Study Design

The TIGE-Rus is designed as a prospective, parallel, two-armed, randomized controlled trial with a 1:1 allocation.

This study will consist of three stages (Figure 1).

The first stage will be a selection of patients with IBD after treatment in the Gastroenterology Department of the Sechenov University Hospital and random assignment of participants to two groups: face-to-face outpatient observation (control group) and observation using telemedicine technologies (intervention group). For every included patient, evaluation of disease activity, QoL, medication adherence, psychological well-being, and satisfaction with medical care will be performed (Figure 1).

The second stage consists of the follow-up care. For the control group, the follow-up scheme includes face-to-face appointment and follow-up recommendations on treatment, post-discharge care plan, and diet. They will be provided with the recommendations on discharge from the hospital and then on the patient’s request. The follow-up for the intervention group consists of the following: monthly completion of questionnaires on the specialized web platform by the patient; the possibility of contacting the gastroenterologist via chat or phone call on the patient’s request; and access to educational information about IBD, psychological well-being, lifestyle, diet, sexual life, pregnancy (examples in Multimedia Appendix A), posted on the web platform. In addition, patients in the intervention group will receive a monthly phone call to address any questions or concerns they may have. During these calls, they will also be interviewed using a predefined checklist (Multimedia Appendix B).

The third stage of the study will be evaluation and comparison of follow-up efficacy in the control and intervention groups. All patients will be re-hospitalized to the Gastroenterology Department after 6 months of follow-up, where the QoL, disease activity, number of IBD relapses, frequency of leukopenia in patients receiving immunomodulators, medication adherence, psychological well-being, and satisfaction with medical care will be assessed (Figure 1).

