### 2.5. Trial Interventions and Participant Timeline

#### 2.5.1. Stage 1

All participants will undergo a series of laboratory tests, including a complete blood count, C-reactive protein levels, and fecal calprotectin. They will also receive instrumental evaluations such as a colonoscopy with biopsy. For patients with severe IBD or jejunoileitis, a contrast-enhanced abdominal and pelvic CT scan or magnetic resonance enterography will be conducted (Table 1).

After group assignment and signing informed consent, all participants will fill out the following questionnaires:Simple Clinical Colitis Activity Index (SCCAI) [15] questionnaire for patients with ulcerative colitis/Harvey-Bradshaw index (HBI) [16] questionnaire for patients with Crohn’s disease;Short Inflammatory Bowel Disease Questionnaire (SIBDQ) [17];World Health Organization’s QoL (WHOQOL-26) [18];General Medication Adherence Scale (GMAS) [19]Patient Satisfaction Questionnaire (PSQ-18) [20];Hospital Anxiety and Depression Scale (HADS) [21];Visceral Sensitivity Index (VSI) [22];Toronto Alexithymia Scale (TAS-26) [23].

The clinical activity of the disease will be measured by Disease Activity Index (DAI) for ulcerative colitis and Crohn’s Disease Activity Index (CDAI) for Crohn’s disease [24,25].

#### 2.5.2. Stage 2

The patients in the control group will have a face-to-face consultation with a gastroenterologist, who will offer treatment recommendations, a post-discharge care plan, and dietary advice. Standard care for the control group will follow evidence-based guidelines, with outpatient visits available upon the patient’s request [24,25].

The telemonitoring group patients will receive authorized access to the personal account on the web platform. The structure of the web platform is shown on the Figure 2. It includes educational content on IBD, necessary lifestyle adjustments, and dietary guidelines, all based on international standards and resources from the Crohn’s and Colitis Foundation.

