Patients will be required to log in to the web platform at least once per month. Upon logging in, they will need to provide the following information: (1) SCCAI for ulcerative colitis and the Harvey-Bradshaw index for Crohn’s disease to assess disease activity during monitoring; (2) the IBD disk questionnaire to track disease progression; and (3) results from laboratory tests (complete blood count, C-reactive protein, and fecal calprotectin). Both healthcare professionals and patients will have access to the test results. Additionally, patients can request an online consultation with a gastroenterologist via chat or phone call. They will be advised to contact a gastroenterologist if they experience disease recurrence.

Each month, gastroenterologists will call patients in the intervention group and ask questions based on a checklist (Multimedia Appendix A). They will be trained to provide immediate assistance if there are critical deviations in health indicators from the reference values (see Table 2) or complaints suggesting the onset of an acute condition.

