**Figure 2 jcm-13-07734-f002:**
[figure not shown]
An online platform structure for patients in the intervention group.

**Table 1 jcm-13-07734-t001:** Summarizes the trial interventions and participant timeline.

	Study Period						
	Enrolment/Baseline 0 Weeks	Follow-Up					End of the Study (6 Months)
		1 Month	2 Months	3 Months	4 Months	5 Months	
Informed consent	X						
Eligibility criteria	X						
Demographic data	X						
Treatment in the Gastroenterology Department	X						X
Adverse events		X	X	X	X	X	X
Treatment	X	X	X	X	X	X	X
Face-to-face consultation for both groups	X						X
Observation using telemedicine technologies for the intervention group (including web-platform, phone calls)		X	X	X	X	X	
Clinical parameters							
Haemoglobin concentration	X	X	X	X	X	X	X
White blood cells concentration	X	X	X	X	X	X	X
C-reactive protein concentration	X			X			X
Fecal calprotectin concentration	X			X			X
IBD disk		X	X	X	X	X	
HBI/SCCAI questionnaire	X	X	X	X	X	X	X
Disease severity according to laboratory and instrumental data	X						X
Disease severity according to CDAI/UCDAI	X						X
Social parameters							
VSI questionnaire	X						X
TAS-26 questionnaire	X						X
HADS questionnaire	X						X
SIBDQ questionnaire	X						X
WHOQOL-26 questionnaire	X						X
Organizational parameters							
PSQ-18 questionnaire	X						X
GMAS questionnaire	X						X

**Table 2 jcm-13-07734-t002:** Limit values of the laboratory tests.

Laboratory Parameter	Critical Deviation from Reference Values
Haemoglobin concentration	Lower than 110 g/L; higher than 170 g/L
White blood cells concentration	Lower than 3 × 10^9^ cells/L; higher than 11 × 10^9^ cells/L
C-reactive protein concentration	Higher than 10 mg/L
Fecal calprotectin concentration	Higher than 200 µg/g for patients included in the trial with initially normal levels. Maintaining the level of more than 800 µg/g between two time points (Table 1) for patients included in the trial with initially high levels

**Table 3 jcm-13-07734-t003:** Study outcomes and data collection methods.

Item	Definition	Data Collection Method	Measure
Primary outcome			
Health-related quality of life (HRQol) in IBD	QoL specifically associated with bowel symptoms	SIBDQ score	Min score is 10, max score is 70. <50 means poor HRQol; >50 optimal HRQol Higher score means better outcome
Secondary outcomes			

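### The six-month relapse comparison is exposed to unequal ascertainment: the text describes interim symptom collection only in the telemonitoring arm, and Table 1 does not agree with it

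*Protocol article*

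**What the plan says.** All references are to the protocol article.

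- **Relapse is a stated comparison.** The Introduction gives as the first of three hypothesised improvements "Clinical aspects: a reduction in the number of relapses and in disease activity". The Objectives repeat it: "Secondary objectives include evaluating disease activity, the incidence of IBD relapses". Section 2.1 places the assessment at the six-month readmission of all patients, "where the QoL, disease activity, number of IBD relapses, frequency of leukopenia in patients receiving immunomodulators".
- **Telemonitoring arm between the two admissions (section 2.5.2).** "Patients will be required to log in to the web platform at least once per month", entering SCCAI or HBI, the IBD disk and laboratory results. A gastroenterologist also calls each month with a checklist; Appendix B shows that it covers stool frequency, blood, weight loss and fever. On flares the section says: "They will be advised to contact a gastroenterologist if they experience disease recurrence".
- **Control arm over the same period.** Section 2.1 gives recommendations at discharge and then at the patient's request. Section 2.5.2 describes standard care "with outpatient visits available upon the patient’s request". Table 1 schedules the face-to-face consultation at baseline and month 6 only.
- **Table 1.** The row "HBI/SCCAI questionnaire" is marked at baseline, at each of months 1 to 5 and at month 6, with no arm named.
- **Outcome tables.** Relapse appears in neither Table 3 nor Table 4. Section 2.7 has outcome variables assessed at baseline and six months.

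**The concern.** The number of relapses over six months is cumulative. Activity scores taken only at baseline and month 6 cannot supply it, so the count has to draw on something that covers the interval: interim reports, clinical records or recall. The text describes a systematic interim route for one arm only. A flare that starts and settles between months 1 and 5 would come to light prospectively in the telemonitoring arm. In the control arm it would come to light only if the patient sought care or remembered it at readmission.

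At stake is a headline clinical hypothesis. If whatever the platform and calls turn up is counted, a real reduction could be hidden, or telemonitoring could seem to cause relapses because it finds more of them. If only recorded visits are counted, flares settled by chat or phone could leave fewer entries than control flares that led to a requested visit, and telemonitoring could look better than it is.

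**Working it through.** **Step 1. The plan's own figure.** The article gives no relapse rate, detection rate or power for relapse. Its only sample-size figure is for SIBDQ (section 2.8): difference 10, SD 12.52, two-sided 0.05, power 80%, loss 20%.

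n per arm = 2 × (1.960 + 0.842)² × 12.52² / 10² = 24.6, so 25. Then 25 / 0.80 = 31.25, so 32 per arm and 64 in total.

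This reproduces the stated 64. (An exact t-test calculation gives 26 per arm and 66 in total, a negligible difference.) SIBDQ is taken at baseline and month 6 in both arms, so this point does not touch it.

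**Step 2. The described routes side by side.**

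| Route to learning of a relapse, months 1 to 5 | Telemonitoring | Control |
|---|---|---|
| SCCAI/HBI | at least monthly on the platform (2.5.2) | none described in the text; Table 1 row has no arm label |
| Clinician's symptom checklist | monthly call (2.5.2, Appendix B) | none described |
| Advice to report recurrence | stated (2.5.2) | not stated |
| Visit | on request, by chat or phone | on request, outpatient |

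Table 1 does not settle the second column. Its telemedicine row is expressly limited to the intervention group, which suggests that unlabelled rows cover both arms. But the IBD disk row is also unlabelled, and the text collects the IBD disk only on the platform. Table 1 and section 2.5.2 therefore cannot both be read at face value.

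**Step 3. Illustration of size (assumptions, not document figures).** Treat relapse as the proportion with at least one recorded relapse, and let recorded risk = true risk × share detected. Assume 95% detection with telemonitoring and 50%, 70% or 90% in controls. With equal true risks, the observed risk ratio is 0.95 divided by control detection. The break-even true ratio, at which the arms look equal, is its inverse.

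| Control detection | Recorded risk at true 30% in both arms | Observed ratio, no true effect | True cut needed to look equal |
|---|---|---|---|
| 50% | 28.5% v 15.0% | 1.90 | 1 − 0.50/0.95 = 47% |
| 70% | 28.5% v 21.0% | 1.36 | 1 − 0.70/0.95 = 26% |
| 90% | 28.5% v 27.0% | 1.06 | 1 − 0.90/0.95 = 5% |

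**Step 4. Effect on a test.** The article names no test for relapse. Section 2.9 uses Fisher's exact test for qualitative variables, so that is assumed, two-sided at 0.05 with 32 per arm.

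- No true effect, true risk 20% to 40%: telemonitoring is declared significantly worse in 8.9% to 27.2% of trials at 50% control detection, 3.8% to 8.9% at 70%, and 1.5% to 2.2% at 90%.
- True halving, control risk 30% to 40%: the chance of showing the benefit is 19.8% to 30.6% with equal 95% detection, 5.6% to 8.5% at 70% control detection, and 1.2% to 1.5% at 50%.

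Even with equal detection, power for relapse is low.

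**Step 5. The other direction.** If the source were recorded visits and the same detection shares applied with the arms exchanged, the observed ratio under no effect would be 0.50/0.95 = 0.53, 0.70/0.95 = 0.74 or 0.90/0.95 = 0.95, in favour of telemonitoring. The sign depends on the source, which is not stated.

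**The case against.** A reader might infer that the relapse count is biased against telemonitoring. The article does not support that as a fact, for four reasons.

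- Nothing says that platform or call data feed the between-arm count. Sections 2.1 and 2.7 place assessment at month 6, in section 2.1 for all patients. An equal history taken at that visit would shrink the problem. This stands, although no such history is described.
- Read literally, Table 1 may mean that control patients also return HBI/SCCAI monthly, and section 2.6 records adverse events at any time point in either arm. So absence of control data is not established. But no route for control patients to return the index is described, and section 2.6 does not say that relapses are counted from adverse events. What stands is an unreconciled conflict.
- The direction is not fixed. Table 3 takes unscheduled visits, surgery and hospitalizations from the electronic health record. If relapse were taken from there too, remote handling of flares could favour telemonitoring. This stands.
- Relapse has no row in Tables 3 and 4, and section 2.9 ties hypothesis tests to Table 4, so no formal relapse test is specified. An article may also leave an operational definition to the full protocol or analysis plan. That is fair, and the point does not rest on a missing definition. It rests on the contact schedule that the article does state. A later plan can restrict the comparison to symmetric sources, but it cannot recover control-arm information that was never collected.

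**Conclusion.** The concern holds as exposure to differential ascertainment, not as a demonstrated bias. As the text describes it, the arms differ sharply in how a relapse between the two admissions would become known; Table 1 points differently on HBI/SCCAI; and no source for the relapse count is given. The bias would probably run against telemonitoring if platform or call findings are counted, and possibly in its favour if only recorded visits are.

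Its size cannot be computed from the document. The observed ratios of 1.06 to 1.90 under no effect rest wholly on assumed detection of 95% against 50% to 90%, and the mirror-image range is equally assumed. The range is wide enough that the relapse result could be uninterpretable, or hardly affected. The primary outcome is untouched. The point merits correction because relapse is part of a headline hypothesis and the remedy is cheap; confidence is medium.

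**What to change.** 1. Reconcile Table 1 with section 2.5.2: state whether control patients return HBI/SCCAI monthly and, if so, by what route. Label the rows by arm.
2. If they do, count relapse from that index in both arms under a single definition, and report the return rate by arm.
3. If they do not, base the between-arm comparison only on information gathered identically in both arms at the existing month-6 readmission: one structured relapse history plus record review, under a single definition and completed without platform or call data. State that the monthly HBI/SCCAI entries do not feed this comparison.
4. In either case, report relapses found only through the platform or calls separately, as a description of the telemonitoring arm.
5. Enter the definition and source in Table 3 and section 2.7.

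**Cost.** If option 3 applies, one short form at a visit that already takes place, plus a few lines of text and table labels. There is no change to care or to the sample size.

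**What remains under option 3.** Mild flares will be missed. Sensitivity need not fall equally: monthly prompting may improve recall in the telemonitoring arm, and flares found by a call may be written into the clinical record that is later reviewed. Both should be stated as residual limitations.

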### 2.2. Study Setting and Eligibility Criteria

The study will be conducted in the Gastroenterology Department of the Sechenov University Hospital in Moscow, Russia. It is a national center where patients from all Russian regions are treated. Thus, the study results can be extrapolated to the entire Russian population.

